**Fig. 1 Fig1:**
[figure not shown]
Map of Tiebissou department, central Côte d’Ivoire. Source of map: own from the study investigators ([name])

There is one main malaria season from May to November. The Lacs district is characterised by intense indoor malaria transmission with a prevalence of malaria reaching 51.3% in children under 5 years old, according to the DHS conducted in 2021 [15]. Net usage for the same period and age group in the Lacs district was 55.3%.

Recent data in a neighboring district showed extremely high resistance intensity (> 1500-fold) to the pyrethroid deltamethrin in *An. gambiae* s.s. and *An. coluzzii*, and < 30% mortality after exposure to py-LLIN. The 1014F kdr mutation was almost fixed (≥ 90%). The carbamate and organophosphate resistance‐associated Ace-1 G119S mutation was also detected at moderate frequencies (22–43%). Transcriptomic analysis identified overexpression of P450 genes (i.e. Cyp6P3 expression up to 33-fold) [17, 23]. Data collected in 2021 by VectorLink demonstrated susceptibility of local vectors to chlorfenapyr in the Gbeke region [24].

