To determine insecticide resistance profiles at baseline and at 12 months post intervention, *Anopheles* larvae will be collected from 3 clusters per trial arm c, reared to adult and exposed to different insecticides. WHO cylinder tests and CDC bottle bioassays will be performed using diagnostic concentrations (DCs) of alpha-cypermethrin, PBO + alpha-cypermethrin, and chlorfenapyr. In addition, CDC resistance intensity bioassays for alpha-cypermethrin and PBO + alpha-cypermethrin (5, 10 or higher x DD) will be performed. Whole transcriptomic characterisation (RNA-seq) will be used to identify highly over-expressed genes per phenotype and will form the basis of site-specific qRT-PCR panels for post-intervention (and wider population-level) resistance monitoring. Illumina whole genome sequencing will be used to identify genetic variants (single-nucleotide polymorphisms and/or copy-number variants), associated per phenotype and will form the basis of site-specific amplicon-seq panels for post-intervention (and wider population-level) resistance monitoring.

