For whole transcriptomic sequencing, total RNA will be isolated from pools of 5–10 *An. gambiae* s.s., *An. coluzzii*, or *An. funestus* s.s., per phenotypic group (i.e. “resistant”—survived exposure to five or ten times the discriminating insecticide concentration; or “unexposed”—mosquitoes from the same field population, which were not exposed to insecticide in control bioassays) and used to prepare RNA-seq libraries for next-generation sequencing, following ribosomal RNA depletion. To obtain sufficient sequencing coverage and depth, our previous RNA-seq experiments have typically comprised nine libraries (two wild populations in technical triplicate and one susceptible colony comparator, also in triplicate—either *An. gambiae* s.s. Kisumu, *An. coluzzii* N’Gousso, or *An. funestus* s.s. FANG), sequenced at 2 × 125 bp paired-end reads on an Illumina Hi-Seq platform [18]. Following sequencing read alignment to annotated reference transcriptome assemblies, available from VectorBase [43] differentially expressed genes (DEGs) will be identified using the standardised DESeq2 pipeline [44]. To account for induction of gene expression during insecticide bioassays, pairwise comparisons of DEGs between “unexposed” field mosquitoes and “susceptible” colony mosquitoes will allow for the identification of significantly over- or under-expressed RNA transcripts, which are associated with constitutive resistance, while comparisons between “resistant” field mosquitoes and “unexposed” field mosquitoes will detect changes in gene expression in response to chemical exposure. Candidate genes, implicated in particular resistance profiles, will be validated by real-time quantitative PCR (RT-qPCR) and developed into multiplex TaqMan RT-qPCR assays to use for surveillance of insecticide resistance selection and changes in relative intervention performance in the cRCT [45].

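### The RNA-seq contrast of bioassay survivors with unexposed mosquitoes is read as a response to exposure, but it also reflects selection on survival, so survival-linked constitutive genes may be misread as induced

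*Protocol article*

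**What the plan says.** The RNA-seq plan is in the Protocol article under Statistical methods {20a}, Secondary outcomes. The resistant group is defined as mosquitoes that "survived exposure to five or ten times the discriminating insecticide concentration". The unexposed group is "mosquitoes from the same field population, which were not exposed to insecticide in control bioassays". A susceptible laboratory colony is the third group.

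Two contrasts are planned, introduced with the aim "To account for induction of gene expression during insecticide bioassays". Unexposed field v susceptible colony is to find transcripts "which are associated with constitutive resistance". Resistant field v unexposed field "will detect changes in gene expression in response to chemical exposure".

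On markers, the same section says: "Candidate genes, implicated in particular resistance profiles, will be validated by real-time quantitative PCR (RT-qPCR"), after which they become multiplex surveillance assays. The Entomology activities section says that RNA-seq "will be used to identify highly over-expressed genes per phenotype", and that these genes form the basis of the site-specific qRT-PCR panels. Tertiary objectives include monitoring selection for resistance mechanisms over time and between arms.

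**The concern.** The resistant group has been exposed, and it has also been filtered, because every mosquito that died has been removed. The unexposed group still contains those that would have died. A gene that is constitutively higher in tolerant mosquitoes will be higher among survivors even if the insecticide changes no expression at all. The protocol gives the whole difference to exposure.

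The stated purpose of the pair of contrasts is to separate induced from constitutive expression, so the reading goes to the heart of what they are for. A constitutive gene tied to survival is a natural marker of selection between arms, whereas a purely induced gene mainly reflects recent contact with insecticide. Mistaking one for the other would misstate the resistance mechanism at the trial site.

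**Working it through.** The protocol states no figure on this point, so there is none to reproduce. The check has two parts: what each contrast compares, and how large the selection effect could be.

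**1. What differs within each contrast**

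| Contrast | Exposure differs | Selection on survival differs | Reading in the protocol |
|---|---|---|---|
| Unexposed field v colony | No | No (but wild v laboratory background does) | Associated with constitutive resistance |
| Resistant v unexposed field | Yes | Yes | Response to exposure |

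No group is listed that was exposed but not selected on survival, so the second row cannot be split into its two parts. The first contrast does not repair this, because it does not compare survivors with non-survivors within the field population. The whole-genome sequencing paragraph that follows sets mosquitoes meeting the same survivor definition against mosquitoes that died, in order to find variants. There, survival is treated as a selected phenotype.

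**2. Ceiling on the selection effect**

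Let s be the share surviving the dose, and suppose there is no induction. The unexposed mean is s × (mean in would-be survivors) + (1 − s) × (mean in would-be dead). Expression cannot be negative, so the unexposed mean is at least s × (survivor mean), and the survivor-to-unexposed ratio is at most 1/s.

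**3. Two models below that ceiling (all inputs assumed)**

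- *Two-class model.* A gene is F-fold higher in every survivor than in every non-survivor, and the colony sits at the non-survivor level. Resistant v unexposed = F/(sF + 1 − s). Unexposed v colony = sF + 1 − s. F = 5 is used below.
- *Graded model.* Natural-log expression is normal with SD σ and correlation ρ with a normal tolerance scale. Resistant v unexposed = Φ(ρσ + z(s))/s, where z(s) is the standard normal quantile at s. The range runs from (ρ 0.5, σ 0.7) to (ρ 0.8, σ 1.0).

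| s | Ceiling 1/s | Two-class, resistant v unexposed | Two-class, unexposed v colony | Graded, resistant v unexposed |
|---|---|---|---|---|
| 0.9 | 1.11 | 5/4.6 = 1.09 | 4.6 | 1.05–1.09 |
| 0.7 | 1.43 | 5/3.8 = 1.32 | 3.8 | 1.16–1.30 |
| 0.5 | 2.00 | 5/3.0 = 1.67 | 3.0 | 1.27–1.58 |
| 0.3 | 3.33 | 5/2.2 = 2.27 | 2.2 | 1.44–2.03 |
| 0.1 | 10.0 | 5/1.4 = 3.57 | 1.4 | 1.76–3.15 |

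With ρ = 0 the graded ratio is 1.00 at every s, so a gene unrelated to tolerance shows no shift. Neither does a gene raised equally in the whole field population.

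**4. What is known about s**

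Survival at five or ten times the discriminating concentration is not given. The nearest figure is under Study setting {9}: "< 30% mortality after exposure to py-LLIN" in a neighbouring district, that is, survival above 70%. At s = 0.7 the ceiling is 1/0.7 = 1.43. That is a different exposure, so it is only a hint. Entomology activities also plans intensity assays with PBO plus alpha-cypermethrin; if the synergist lowers survival, the lower rows of the table become relevant.

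**The case against.** The strongest reply is that nothing follows for the markers. A reader might infer that survival-linked constitutive genes will be dropped as induced and that the panel will fill with field-v-laboratory background. The documents do not support that. Neither marker rule admits or drops a gene by an induced or constitutive label, and under the Entomology activities rule a gene raised in survivors is a candidate whatever its mechanism. In the two-class model the same gene also appears in unexposed v colony, at 2.2- to 4.6-fold for s from 0.3 to 0.9. At s = 0.1, where that contrast falls to 1.4, the gene shows 3.57-fold in survivors. This part of the objection stands.

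It is also fair that large effects need low survival. The 3.57-fold value needs 10% survival, which nothing in the documents suggests, and a gene that separates survivors perfectly. Nor does the protocol overclaim for the colony contrast: it says only that those transcripts are associated with constitutive resistance, not that background differences are excluded. The genome-sequencing arm and the phenotypic bioassays give further, separate evidence on resistance.

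What the objection does not remove is the sentence itself. Whenever survival is below 100% and a gene's expression varies with tolerance, the contrast contains selection as well as any induction, and the stated reading leaves selection out.

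**Conclusion.** The point holds as an error of interpretation. Resistant v unexposed confounds induction with selection on survival, so constitutive genes linked to survival may be misread as induced. Whether they will be, and by how much, is not known. The selection effect is at most about 1.1-fold at 90% survival, 1.4-fold at 70% and 3.3-fold at 30%, and the protocol does not give the relevant survival. The ceiling assumes only non-negative expression and no induction; the model values rest on the assumed F, ρ and σ.

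The consequence is limited to the inferred mechanism in an exploratory, marker-finding outcome. The Abstract lists genotypic resistance with the secondary outcomes, while Tertiary objectives and Outcomes {12} place it lower. Either way, the comparisons of malaria incidence, infection prevalence, vector density and EIR do not depend on it. This is a minor point that is worth correcting because the correction is nearly free.

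**What to change.** In the RNA-seq paragraph under Statistical methods {20a}, Secondary outcomes:

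- Describe resistant v unexposed as showing *induced and/or survival-associated* expression.
- Report resistant v colony beside the two planned contrasts, from the same libraries. It helps detection but does not separate induction from selection: its fold change is the product of the other two (in the two-class model at s = 0.7, 1.32 × 3.8 ≈ 5).
- State that no gene will be called induced, or set aside as induced, on resistant v unexposed alone. A firm claim of induction would need an exposed group not selected on survival, which is not among the listed groups.

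A rule giving panel priority to genes that are also raised in resistant v unexposed may look attractive but should not be adopted. It would demote resistance genes that are uniformly over-expressed in the field population, since these show little or no shift in that contrast.

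The cost is one extra DESeq2 contrast and a more cautious mechanistic statement, with no new mosquitoes or sequencing.

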### Interim analyses {21b}

There will be no interim analyses. The Data Safety Monitoring Committee (DSMB) will have access to the data to ensure that the study is appropriately powered and that no adverse events are occurring due to the intervention.

### Methods for additional analyses (e.g. subgroup analyses) {20b}

The impact of covariates such as baseline prevalence age of child, gender, socio-economic status, distance to health facility, etc. on malaria incidence will be analysed, where regression is carried out on the individual-level data (ignoring the clusters) and then comparing the residuals for each cluster based on the observed outcome, compared to the predicted outcome, in the absence of an intervention effect. Comparison of the residuals using a *t*-test will provide a measure of intervention effect, adjusted for covariates.

For malaria infection prevalence data, subgroup analysis will include investigating individual level, household level, distance to health facility, and cluster-level characteristics, such as age group, socio-economic status, household construction, vector species composition, cluster net coverage, and insecticide resistance intensity. These analyses will be performed on the residuals of the cluster-level results, as documented for the incidence analyses. Secondary analyses with EIR data will include adjusting for timepoint and comparing residuals of the cluster-level summaries.

Where possible, geospatial models of vector species distribution and insecticide resistance across the study area will be developed using machine learning algorithms incorporating entomological field indices linked to the point locations of vector sampling alongside earth observation data on relevant covariates (e.g. climate, vegetation indices, elevation, land cover/land use, population density).

### Methods in analysis to handle protocol non-adherence and any statistical methods to handle missing data {20c}

We do not expect that there will be significant cross-over (by having a minimum distance of 2 km between study clusters, thereby creating buffers between study clusters) or loss to follow-up. Hence, further analyses to account for these factors should be very similar to the ITT analyses. Separate analyses will be done looking at regular net users compared to those who report irregular use, that is, < 75% reported usage the previous night over the entire follow-up duration. During cross-sectional surveys, separate analyses will be performed to compare people reporting the use of the correct net the previous night to those who did not.

Reasons for withdrawal from each treatment arm will be reported and the reasons compared qualitatively. Missing data will be described in each arm and possible biases due to missing data discussed. Data analyses will be performed on complete cases. The possible effect of missing data on study results will be evaluated in sensitivity analysis.

### Plans to give access to the full protocol, participant-level data, and statistical code {31c}

The full protocol, future participant-level dataset, and statistical code will be available on reasonable request.

## Oversight and monitoring

### Composition of the coordinating centre and trial steering committee {5d}

A Trial Steering Committee (TSC) of three Africa-based experts in Entomology and Epidemiology with considerable experience of vector control trials will be established to provide oversight for the study. The TSC members will be independent of the trial and its institutions and have the necessary expertise to monitor study progress and participant safety. They will meet remotely every 6 months to get an update on the trial. The coordinating centre will be run by an experienced management team, a trial manager, data manager, and field teams.

### Composition of the data monitoring committee, its role and reporting structure {21a}

A DSMC will be established to provide oversight for the study. This committee will be made up of three expert Statisticians and Epidemiologists, with experience in analysing trial data. DSMC members will be independent of the trial and its institutions and have the necessary expertise to monitor study progress and participant safety. The DSMC will be responsible for monitoring the progress of the trial, adherence to the protocol, the safety data, and the critical efficacy endpoints. Members will meet remotely or in-person every 6 months.

### Adverse event reporting and harms {22}

Although the risk to study participants is considered minimal from any of the study LLINs, we will still document their safety. Any adverse events which have been reported previously to be associated with exposure to insecticides such as skin rashes, skin burning, skin itching, skin paraesthesia, eye tearing, watering eyes, runny nose, sneezing, mucosal irritation, headache dizziness, and their severity will be monitored in the study cohort and study participants selected during the cross-sectional survey. We will also record other AEs and SAEs will be collected during follow-up of the cohort children by non-directive questions during the follow-up visits and through volunteer reporting in the study population. Study staff will record any AEs in the AE report form and immediately report to the study clinician. Excessive clustering of SAEs will be reported to DSMC, TSC, and IRB. Study personnel will be trained to recognise and report AES.

The trial will follow standard definition for AEs and SAEs [48]:Adverse events: any untoward medical occurrence in a patient or clinical investigation subject administered a pharmaceutical product and which does not necessarily have to have a causal relationship with this treatment.A serious adverse event (experience) or reaction is any untoward medical occurrence that at any dose: (1) results in death, (2) is life-threatening, (3) requires inpatient hospitalisation or prolongation of existing hospitalisation, (4) results in persistent or significant disability/incapacity, or (5) is a congenital anomaly/birth defect.

### Frequency and plans for auditing trial conduct {23}

The trial management team will be responsible for trial conduct and will report to the TSC at regular timepoints throughout the trial. The TSC are independent from the study sponsor and investigators.

### Plans for communicating important protocol amendments to relevant parties (e.g. trial participants, ethical committees) {25}

Any amendments to the study protocol and informed consent forms will be submitted for approval to both IRBs. The funder and sponsor will be notified of any changes to the protocol, as well as the TSC and DSMC. A copy of the amended protocol will be added to the Trial Master File. Protocol deviations and/or violations will be documented using protocol deviation notification forms.

#### Patient public involvement

There was no patient or public involvement in the design of this protocol.

### Dissemination plans {31a}

Quarterly progress reports will be shared with district and NMCP officials to disseminate project findings and improve malaria knowledge, local strategy, and LLIN usage. An end of project workshop with MOH, NMCP, implementing partner, and funders will be organised to share study findings and translate into future vector control strategy. Mid- and end of project meetings will be held to share progress and results with village and community leaders to help disseminate findings to the community. Keynote presentations by project researchers at international scientific conferences will be done to present study findings to the international malaria control community.

## Discussion

There is a paucity of data on the efficacy of pyrethroid-PBO LLINs on malaria case incidence and malaria infection prevalence, especially in West Africa, where vectors tend to exhibit high levels of insecticide resistance and mechanisms of resistance may differ from those in East African vector populations. The efficacy of chlorfenapyr-py LLINs compared to standard py-LLIN has been demonstrated in cRCTs in Tanzania [12] and in Benin [13] over a 2-year follow-up period. This led to the WHO revising its recommendations earlier this year. The WHO now strongly recommends the use of chlorfenapyr-py LLINs instead of standard py-only LLIN in areas with insecticide-resistant malaria vectors [14]. However, there is still a lack of evidence on the efficacy of py-PBO LLINs compared to standard py-only LLIN in West Africa on epidemiological and entomological outcomes. In previous trials, PBO-pyrethroid nets seemed to have marginal superiority over pyrethroid-only nets at 24 months post net distribution [7, 12, 13].

To the best of our knowledge, this will be the first trial of py-PBO nets in West Africa. This will add to the existing body of literature by providing much needed data in this high-transmission setting. The results of this trial will be used by the WHO for informing malaria control policies in West Africa.

## Trial status

Protocol version 1.1 of December 08 2022. Participant recruitment has not begun. Participant recruitment is estimated to end June 30, 2024.

## Data Availability

The Principal Investigator (PI), [name] and Co-PI [name], will have full access to all the data in the study and will have final responsibility for the decision to submit for publication.

## Abbreviations

AE: Adverse event
AI: Active ingredient
CFP: Chlorfenapyr
CFP-py: Chlorfenapyr-pyrethroid
COV: Coefficient of variation
cRCT: Cluster randomised control trial
CRF: Case report form
DHS: Demographic health survey
DSMC: Data safety monitoring committee
EIR: Entomologic inoculation rate
ELISA: Enzyme-linked immunosorbent assay
GIS: Geographical information systems
GPS: Global positioning system
ICC: Intra-cluster correlation coefficient
IEC: Information, education, communication
IG2: Interceptor G2
INSP: Institut National de Santé Publique
IPR: Institut Pierre Richet
IRB: Institutional review board
ITT: Intention to treat
HLC: Human landing catch
LLIN: Long-lasting insecticidal net
LSHTM: London School of Hygiene and Tropical Medicine
NMCP: National Malaria Control Program
ODK: Open Data Kit
PBO: Piperonyl butoxide
PBO-py: Piperonyl butoxide- pyrethroid
PCR: Polymerase chain reaction
Py: Pyrethroid
RDT: Rapid diagnostic test
RR: Rate ratio
SAE: Serious adverse event
SOP: Standard operating procedure
SSA: Sub-Saharan Africa
TSC: Trial steering committee
WHO: World Health Organization
